### Administration of measures

Demographic characteristics were assessed using administrative records, the screening interview, and the enrollment interview. Pain severity was evaluated with VAS (visual analog scale (zero to ten) on the Changhai pain scale, where zero represents no pain and ten unbearable pain. The scale chosen for pain assessment was categorized as mild (VAS 0 to 4.0), moderate (VAS 4.1 to 6.0) and severe (VAS >6.1)). Physiological parameters: heart rate, blood pressure and digital oxygen saturation were monitored with Infinity Vista XL (Draeger Medial Systems Inc., Danvers, MA, USA). Psychological reactions were measured with the C-BSPAS using five items focusing on dressing-pain-related anxiety. Patient’s satisfaction and the health care professional’s acceptance of diluted nitrous oxide on burn dressing analgesia were audio recorded with an aigo R5518 digital voice recorder (aigo Digital Technology Co. Ltd., Beijing, China). Clinical data, including burns diagnosis, analgesic prescription and hospital cost were obtained via a chart review using a standardized form.

### Sample size determination

A prospective sample size calculation was performed by a senior academic statistician using SAS POWER procedure during the protocol-writing stage. It aimed to determine a target sample size that would provide 90% power for two-tailed testing (at a type-1 error rate of 5%) of each of the measures. According to the result of our preliminary study, a sample size of 12 was targeted as being sufficient to achieve the required effective sample size, but to meet the Chinese Food and Drug Administration standard for safety and feasibility of nursing staff implementing this inhalation analgesic, the targeted sample size of 240 was recommended.

### Data safety and monitoring board (DSMB)

The first patient was enrolled on 14 October 2011. A DSMB was established shortly after the project launch and met several times during the data collection period. Members included two pain management specialists; four burns-trained nursing officers and doctors; and a senior academic statistician who served as the Board's chair.

### Planned analytic approach

In subsequent publications, we will report results pertaining to the analgesic effects of NOOM on burn dressing pain. Primary outcomes will include: 1) pain severity during dressing, measured as the mean of average and worst pain, and 2) burns-dressing-induced anxiety. The physiological parameters and satisfaction of both health care providers and patients are considered as secondary outcomes. Finally, exploratory analyses will assess the interaction between the intervention and age, sex, and racial minority. The primary estimates of the effects of the intervention on each of these outcomes will come from repeated measure analyses, following the intent-to-treat principle.

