**Discussion:**

Based on the findings from our previous qualitative study that physician’s reluctance to order narcotic analgesia is due to its adverse effect and from our pilot experiment, this study aims to test the hypothesis that a fixed nitrous oxide/oxygen mixture will promote better burn dressing pain alleviation and outcomes. Analyses will focus on the effects of the experimental intervention on pain severity during dressing (primary outcomes); physiological parameters, C-BSPAS and acceptance of both health care professionals and patients (secondary outcomes). If this model of analgesia for burn pain management implemented by nurses proves successful, it could potentially be implemented widely in hospital and prehospital settings and improve patients’ satisfaction and quality of life.

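### Anxiety (C-BSPAS) is secondary in the abstract but a second primary outcome in the planned analysis, so the article does not fix which result defines success

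*Protocol article*

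**What the plan says.** The article sets out its outcome hierarchy twice.

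- **Abstract, Discussion paragraph:** the analyses will focus on "pain severity during dressing (primary outcomes); physiological parameters, C-BSPAS and acceptance of both health care professionals and patients (secondary outcomes". Pain is the only outcome labelled primary, and C-BSPAS is secondary.
- **Methods, Planned analytic approach:** the primary outcomes are "1) pain severity during dressing, measured as the mean of average and worst pain, and 2) burns-dressing-induced anxiety". The next sentence reads "The physiological parameters and satisfaction of both health care providers and patients are considered as secondary outcomes". Anxiety is in the primary list and absent from the secondary list.

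Two other sections bear on the point.

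- **Administration of measures:** "Psychological reactions were measured with the C-BSPAS using five items focusing on dressing-pain-related anxiety". C-BSPAS is therefore the article's measure of dressing anxiety, and the two lists classify the same outcome differently.
- **Sample size determination:** the calculation aimed at "90% power for two-tailed testing (at a type-1 error rate of 5%) of each of the measures".

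The article does not say whether one or both primary outcomes must be positive for the trial to succeed.

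**The concern.** The primary outcome determines what the trial can conclude. With two incompatible hierarchies in print, a positive anxiety result could be reported as a primary finding by citing the analysis section, and a negative one as a secondary finding by citing the abstract. The article expects both pain and C-BSPAS to favour the nitrous oxide arm, so either could carry the main claim.

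The type-1 error of the primary claim depends on the same choice. The only error rate in the article is 5% two-tailed for each measure. With two primary outcomes and a rule that either suffices, the chance of at least one false positive primary result would exceed 5%. With one primary outcome, or a rule that both are required, it would not.

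**Working it through.** **1. Is it the same outcome under two labels?**

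| Place | Pain during dressing | Dressing anxiety / C-BSPAS |
|---|---|---|
| Abstract, Discussion paragraph | primary | secondary |
| Planned analytic approach | primary | primary; not in the secondary list |

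Administration of measures ties C-BSPAS to dressing anxiety, so the right-hand column is one outcome with two classifications. Neither text is an amendment log or superseded wording.

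**2. The plan's own figure.** The sample size section reports that "a sample size of 12 was targeted as being sufficient to achieve the required effective sample size". This 12 cannot be reproduced, because no effect size or standard deviation is given. As a guide only, 90% power at two-sided 5% with 12 patients in total, split 1:1, needs a standardised difference of 1.87 (normal approximation) or 2.08 (t-test). The target of 240 (180 vs 60) was set on regulatory grounds of safety and feasibility, so it does not show how alpha was meant to be shared.

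**3. Family-wise error if either outcome suffices.** Inputs: two tests, each at two-sided 0.05 (Sample size determination). The correlation r between the test statistics is an assumption, because the article gives none. Under no effect on either outcome,

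FWER = 1 − P(|Z1| < 1.96 and |Z2| < 1.96).

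At r = 0 this is 1 − 0.95² = 0.0975. For r > 0 it comes from the bivariate normal distribution:

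| r | 0 | 0.3 | 0.5 | 0.7 | 0.8 | 0.9 |
|---|---|---|---|---|---|---|
| FWER, 5% each | 0.0975 | 0.0951 | 0.0907 | 0.0835 | 0.0781 | 0.0704 |

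**4. Error under the other readings.**

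- Pain as sole primary outcome, with anxiety secondary or tested only after pain: 0.05 for the primary claim.
- Both required: at most 0.05. With no effect on either outcome, the chance that both are significant is 2 × 0.05 − FWER, which is 0.10 − 0.0975 = 0.0025 at r = 0 and 0.10 − 0.0704 = 0.0296 at r = 0.9.
- Each tested at 2.5%, either suffices: 0.0494 at r = 0, 0.0465 at r = 0.5 and 0.0402 at r = 0.8.

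**5. Cost of a split at 60 vs 180.** Using the normal approximation for two means, the detectable standardised difference at 90% power is d = (z for alpha + 1.2816) × √(1/60 + 1/180), where the root is 0.1491.

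- At 5%: (1.9600 + 1.2816) × 0.1491 = 0.483.
- At 2.5%: (2.2414 + 1.2816) × 0.1491 = 0.525.

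Power at d = 0.5 falls from 91.8% to 86.7%. At d = 0.8 it is above 99.9% either way.

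**The case against.** The strongest reply accepts the conflict in classification and disputes what is built on it.

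- **The error rate.** A reader might infer that the trial's 5% error rate nearly doubles. The article does not support this. Inflation needs a rule that either outcome suffices, and none is stated. It also needs weak correlation to come near doubling. C-BSPAS is recorded in the same patients at the same time points as the pain score and concerns anxiety about that pain, so positive correlation is plausible. This objection stands.
- **The sample size sentence.** It describes what the calculation aimed to provide and is not a decision rule. Powering each measure at 5% is equally consistent with requiring both. This also stands: the sentence shows an unsplit 5% per measure and no more.
- **Multiplicity control.** A reader might infer that the trial has none. This is a journal article, and a testing order or alpha split may be in an analysis plan that is not shown. Silence on that point is not a finding.
- **Prior record.** The trial is registered, and unblinding is to wait until all trials are completed. It cannot be said that no earlier record fixes the primary outcome, nor that the registration is wrong, because it is not at hand.

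None of this removes the contradiction. The article states the primary outcome twice and differently, and an unseen analysis plan cannot make its two sections agree.

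**Conclusion.** The contradiction stands and should be fixed: the abstract and Planned analytic approach disagree on whether dressing anxiety is a primary outcome, and nothing else in the article decides between them. Confidence in this is high, since it rests on the text alone.

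The effect on type-1 error is conditional. If either outcome sufficed at an unadjusted two-sided 5%, the family-wise error would be about 7.0% to 9.75%, over an assumed correlation of 0.9 down to 0. If pain is the sole primary outcome or both are required, it is at most 5%. The article does not say which rule applies, so the higher figures show what is at stake if the ambiguity remains. They are not an established property of the design.

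**What to change.** Before unblinding, amend Planned analytic approach so that pain severity during dressing is the sole primary outcome. This matches the abstract's hierarchy and the stated aim, which the abstract's Background and the main Discussion both frame in terms of pain. Make C-BSPAS the first secondary outcome, tested at two-sided 5% only if pain is significant. The abstract then needs no change.

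If the sponsor prefers two primary outcomes, amend the abstract instead and state one of two rules: both must be significant at 5%, or each is tested at 2.5%.

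In either case, check that the registration agrees with the chosen hierarchy.

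The cost is wording only. Under the fixed sequence, power for pain is unchanged, but anxiety cannot be claimed if pain fails. A split at 2.5% moves the detectable standardised difference at 90% power from 0.48 to 0.53 with 60 vs 180 patients. If both are required, the chance of success can be no higher than the power for the weaker of the two outcomes.

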### Patient eligibility, recruitment, consent, and randomization

Ethical approval was obtained from Shanghai’s Changhai Hospital Ethics Committee (CHEC2011-105). Verbally consenting patients completed a study enrollment pack containing a written consent form and a Chinese versioned burn specific pain anxiety scale (C-BSPAS). Patients eligible for enrollment in the study included all cognitively intact, Chinese speakers aged three to sixty-five from participating burn centers, selected for 1 to 70% of total body surface area (TBSA) burn and who reported moderate to severe burn dressing pain .TBSA was diagnosed by doctors. Moderate pain severity was defined as a score of four or greater (on a scale of zero to ten) for worst pain during dressing. Specific inclusion and exclusion criteria are presented in Table 1.

**Table 1 T1:** Patient inclusion and exclusion criteria

Inclusion Criteria	Exclusion Criteria
Aged 3 to 65, either male or female	Mental disorder, drug dependence and drug abuse
Participants sustained 1-70% of TBSA burns or other injury requiring dressing procedure	Unconscious and unable to express pain by Changhai pain scale (VAS)
Recent worst pain (during dressing) reported to be 4 or higher (on a scale of 0 to 10)	Abdominal distension or suspected bowel obstruction, air embolism, pneumothorax, decompression sickness, epilepsy, chronic obstructive pulmonary disease and acute respiratory infection, pregnancy, severe inhalation injury; pharmaceutical or pathological pulmonary fibrosis; Maxillofacial injuries
The participants are volunteers and written consent obtained	
Burns or injured area not affecting the vital signs and digital pulse oximeter monitoring	Disease involving ear, nose, larynges such as sinuses, middle ear, tympan graft

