### Description of experimental and control interventions

Process of allocation concealment; The experiment was carried out in three centers. The patients were given a number from 1 to 240. A randomization list was produced by a statistician according to our preliminary study. Due to the severity of the pain suffered, ethically it was decided to help as many as possible, so patients given the letters A, B or C were treated using a canister with the appropriate letter containing preprepared NOOM. Those with D were given oxygen only, from an identical-looking canister labeled D. Neither patients, nor doctors, nor nurses, nor data collector knew what was in each canister, thus they were all blind. The nursing officer who implemented the intervention handed the doctors envelopes containing the patients’ name and allocation of A, B, C or D. Thus patients receiving NOOM or oxygen were in the ratio 3:1. A sample size of 240 was established and randomized into two groups, for which patients with at least moderate pain severity (worst pain, visual analog score, VAS > = 4 out of 10) during dressing were randomly assigned to receive usual pain treatment plus oxygen (UTO = 60) and usual pain treatment plus preprepared NOOM (UTN, n = 180) intervention two minutes before dressing based on the current clinical practice, respectively. For each group, intervention outcome including pain severity (VAS), blood pressure (BP), heart rate (HR), digital oxygen saturation (SpO_2_) and C-BSPAS were taken two minutes prior to intervention, during dressing, immediately after dressing, and 10 minutes after dressing. Video and audio recordings were taken individually for later communication coding and outcome analyzing. Rescue analgesic was recorded.

Blinding: The double-blind RCT list was held by a researcher. The researcher (a nursing officer), who held the randomizing list was blind too. The list only showed groups A, B, C and D, but did not indicate what treatment these letters stood for. Oxygen intervention was used as a control group. The rules were that the cessation of blinding would take place only after all the trials had been completed.

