Indicators present for the expected change in pain between the control and treatment interventions will be examined. The anticipated pain score (VAS) during dressing will be reduced to three to five in the UTN group. The physical parameters such as blood pressure, digital oxygen saturation should be maintained within normal range in the treatment group. The anticipated C-BSPAS will be much lower in the treatment group than that in the control group, and both patients’ and doctors’ satisfaction with the use of the treatment intervention should be obtained after dressing.

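### The plan expects blood pressure and oxygen saturation to stay in normal range on the gas mixture, but the repeated-measures contrast it states cannot show whether individual patients did

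*Protocol article*

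**What the plan says.** All of this is in the protocol article.

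- **Expectation.** Among the anticipated results that close the section on experimental and control interventions: "The physical parameters such as blood pressure, digital oxygen saturation should be maintained within normal range in the treatment group". No range is defined.
- **Role and method.** Under Planned analytic approach, "The physiological parameters and satisfaction of both health care providers and patients are considered as secondary outcomes", and "The primary estimates of the effects of the intervention on each of these outcomes will come from repeated measure analyses", by intention to treat.
- **Age.** Table 1 admits patients "Aged 3 to 65, either male or female". Age enters the stated analysis once: "exploratory analyses will assess the interaction between the intervention and age, sex, and racial minority".
- **Readings.** Blood pressure, heart rate and SpO2 "were taken two minutes prior to intervention, during dressing, immediately after dressing, and 10 minutes after dressing", so each patient has a pre-intervention value.
- **Size.** Sample size determination says that 12 patients met the power requirement, and that 240 was recommended "to meet the Chinese Food and Drug Administration standard for safety and feasibility of nursing staff implementing this inhalation analgesic". The arms are 180 NOOM and 60 oxygen.

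**The concern.** Staying within a normal range is met or failed patient by patient. A repeated-measures treatment effect, as usually fitted to a continuous reading, asks whether the arms differ on average. A small share of patients with large falls can leave the arm average looking normal.

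This matters more here than for an ordinary secondary outcome. The stated reason for going from 12 to 240 patients is safety and feasibility of nurse delivery, and the physiological parameters are the only safety-type data among the outcomes the article lists. If the normal-range statement were drawn from the stated estimates, the trial could report that the parameters stayed normal while some patients left the range.

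Age adds a second, narrower difficulty. Normal blood pressure and heart rate differ between a young child and an adult, so a single range applied across ages 3 to 65 would misclassify some readings. This second point does not concern SpO2.

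**Working it through.** **What can be reproduced.** The article gives no figure for the physiological parameters: no range, SD or expected rate. Its sample sizes are not in dispute here. The calculations below illustrate the averaging on assumed values.

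**Inputs from the article.** 180 NOOM and 60 oxygen patients.

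**Assumed inputs.** SpO2 mean 98; between-patient SD s of 1.5 to 3 points; a share f of NOOM patients falls by D = 10 points; no control patient falls.

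**Step 1: shift in the arm mean.** Shift = f × D.

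- f = 2% (3.6 patients): 0.02 × 10 = 0.2, mean 97.8
- f = 5% (9 patients): 0.05 × 10 = 0.5, mean 97.5
- f = 10% (18 patients): 0.10 × 10 = 1.0, mean 97.0

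**Step 2: would a comparison of means detect it?** NOOM variance = s² + f(1 − f)D². SE = √(NOOM variance/180 + s²/60). Power = Φ(shift/SE − 1.96).

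For f = 5% and s = 1.5, the variance is 2.25 + 0.0475 × 100 = 7.0. SE = √(7.0/180 + 2.25/60) = 0.276, and 0.5/0.276 = 1.81. Power = Φ(−0.15) = 44%.

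| Share falling | s = 1.5 | s = 2 | s = 3 |
|---|---|---|---|
| 2% | 13% | 9% | 6% |
| 5% | 44% | 31% | 18% |
| 10% | 89% | 77% | 52% |

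Simulations with SD 1.2, values capped at 100 and a pooled t test gave about 19% to 24% at f = 5%. All of these treat a single time point, not the full repeated-measures model.

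**Step 3: the same patients counted.** 9/180 = 5.0%, Clopper-Pearson 95% CI 2.3% to 9.3%. The chance of seeing at least one case in 180 is 1 − (1 − f)^180, which is 97% at f = 2% and over 99.9% at f = 5%.

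**Step 4: is the count a stronger test?** Not in general. Fisher's exact test for 9/180 v 0/60 gives p = 0.12. Approximate power of the two-proportion comparison is 7%, 36% and 85% at 2%, 5% and 10%, much like the means.

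**Step 5: mixed ages.** Randomisation keeps the arm difference unbiased over ages. Pooling costs precision if neither age nor baseline is used. The difference detectable with 90% power is (1.96 + 1.282) × SD × √(1/60 + 1/180) = 0.483 × SD. For heart rate with an assumed within-age SD of 12, that is 5.8. Adding an assumed between-age SD of 20 gives a total SD of √(144 + 400) = 23.3 and a detectable difference of 11.3.

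**The case against.** The best defence is that the article does not restrict itself to means. It speaks of primary estimates, which leaves room for descriptive and per-patient tables. Repeated-measures methods can also take a binary outcome, and no scale is fixed. The normal-range sentence sits among anticipated results and refers to the treatment group. Limits and table layouts are commonly left to a full protocol or analysis plan, neither of which is shown. A data safety and monitoring board was in place, and a routine table with SD and range would reveal extreme values.

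Much of this stands, and it rules out stronger readings that a reader might infer:

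- **That means are the only analysis, or that values are analysed raw.** The text says neither, and a pre-intervention reading is available to the model.
- **That normal range is a binding per-patient rule.** It is worded as an expectation.
- **That children have no valid reference.** Each child has a baseline, there is a randomised control arm, and an age interaction is planned as exploratory. What is not stated is an age-appropriate range.
- **That pooling ages biases the comparison.** It does not (Step 5).
- **That per-patient counts would detect harm between arms more reliably.** Step 4 shows otherwise.

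What the defence does not remove is the mismatch. The article states both an expectation about a range and a method of estimation, and the method as ordinarily used does not address the expectation. The age interaction asks whether the treatment effect differs by age; it counts nobody out of range. Board oversight during the trial does not supply the reported safety result, and a minimum or SD does not say how many patients were affected.

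**Conclusion.** The concern holds in a limited form: the stated method does not fit the stated expectation for blood pressure and SpO2. The method is legitimate for the between-arm effect; it cannot by itself support a statement that patients stayed within range.

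The size of the masking rests wholly on assumed values. If 5% of NOOM patients fell by 10 SpO2 points, the mean would move 0.5 point, and a comparison of means would detect it in roughly 18% to 44% of trials for SDs of 3 down to 1.5. The direction needs no assumption beyond arithmetic: the shift is the share affected times the fall. The age point is confined to blood pressure and heart rate, and carries no estimate from the article.

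The change is worth making before unblinding because safety and feasibility justify the enlarged trial and the readings are already planned. The point does not call the randomised comparison into question.

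**What to change.** Keep the repeated-measures estimates and add a per-patient summary of the physiological readings.

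1. For SpO2, blood pressure and heart rate, report by arm the number and proportion of patients with any reading after the start of inhalation outside preset limits, with exact 95% CIs.
2. The investigators set the limits before unblinding, age-appropriate for heart rate and blood pressure. Their values are a clinical matter on which this review takes no position.
3. Report change from each patient's own pre-intervention reading alongside.
4. Base any statement that parameters stayed within normal range on these proportions and their upper confidence limits, not on arm means.

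The cost is agreeing limits in advance, a short addition to the analysis wording and a few tables; no new measurement is needed. The safety statement becomes slightly less favourable, because a rate with an upper bound replaces a normal-looking mean.
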